## Abstract

**Background:**

Trauma exposure is pervasive in people with an At Risk Mental State (ARMS) and is associated with adverse clinical and functional outcomes. While promising developments have been made in treating trauma in psychosis, evidence regarding the efficacy of trauma therapies in ARMS individuals is limited. This trial aims to evaluate the feasibility of conducting a future randomised controlled trial (RCT) to determine the efficacy of Eye Movement Desensitisation and Reprocessing (EMDR) and trauma focused cognitive behavioural therapy (TF‐CBT) in people with ARMS.

**Method:**

Seventy ARMS individuals with a history of trauma will be randomised to receive 24 sessions of EMDR plus treatment as usual (TAU), 24 sessions of TF‐CBT+TAU, or TAU alone. Feasibility will be determined against pre‐specified thresholds for recruitment, retention, treatment engagement, and fidelity. To examine the promise of efficacy of EMDR and TF‐CBT, participants will complete a battery of clinical and mechanistic measures at baseline and 9‐month post‐randomisation, including assessments of attenuated psychotic symptoms and post‐traumatic symptoms. Clinical notes will be reviewed to identify transitions to first episode psychosis up to 12 months post‐randomisation. Qualitative interviews with trial participants, therapists, and professional stakeholders will explore the acceptability of EMDR and TF‐CBT and factors to facilitate future implementation of trauma therapies in routine practice.

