### Participants

3.2

This trial will aim to recruit 75 individuals who (1) meet ARMS criteria operationalised using the updated version of the Comprehensive Assessment of At‐Risk Mental States (CAARMS‐23; Yung et al. 2023) and (2) report exposure to past traumatic events in childhood or adulthood on the Trauma and Live Events questionnaire (TALE; Carr et al. 2018). The full inclusion and exclusion criteria of the RCT are listed in Table 1.

**TABLE 1 eip70095-tbl-0001:** Inclusion and exclusion criteria.

Inclusion criteria	16 years of age or older Meeting ARMS criteria as defined by the CAARMS Capacity and willingness to provide informed consent Reported exposure to at least one potentially traumatic life events, as assessed by the TALE
Exclusion criteria	Under 16 years of age Non‐English speaking or requiring an interpreter for the intervention (the assessment battery at present can only be delivered in English) Evidence of recent or past transition from ARMS status to first episode psychosis (FEP), operationally defined as meeting CAARMS transition criteria (i.e., history of a treated or untreated psychotic episode of 1 week's duration or longer) and/or previous or current treatment with antipsychotics at dose of over 5 mg of haloperidol or equivalent for over 3 weeks Judged by the assigned care‐coordinator/responsible clinician and the research team as not sufficiently clinically stable to engage safely in a clinical trial of trauma‐focused therapy (e.g., acutely suicidal and suicide attempt in the previous 2 months; in a current mental health crisis; not in stable housing).

*Note:* ARMS = at risk mental state; CAARMS = comprehensive assessment of at risk mental states (Yung et al. 2005); TALE = Trauma and Life Events checklist (Carr et al. 2018).

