#### Randomisation and Allocation Concealment

3.2.1

Participants will be randomly allocated to either (1) EMDR+TAU, (2) TF‐CBT+TAU, or (3) TAU only at a ratio of 1:1:1. Randomisation will be independent and concealed via an online pseudo‐random list with random permuted blocks of varying sizes. Allocation will be concealed from the RAs conducting follow‐up assessments. If an RA becomes “unblinded” to a participant's allocation during the study, where possible, the participant will be allocated to another RA. Where this is not possible, interview‐based measures will be recorded with participant consent, and the measure will be scored by blinded RAs.

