## Outcomes

5

The RCT is designed to evaluate the feasibility of conducting a future definitive trial. Hence, the trial's primary outcomes will be the key feasibility indicators required to recommend progression towards a future larger‐scale trial (trial recruitment, trial retention, EMDR/TF‐CBT treatment engagement, and EMDR/TF‐CBT treatment fidelity). These will be operationalised according to pre‐specified feasibility thresholds informed by past research on trauma‐focused interventions in people with first episode psychosis (Varese et al. 2024) and approved by an independent Trial Steering Committee (Table 2).

**TABLE 2 eip70095-tbl-0002:** Principal feasibility outcomes and proposed feasibility thresholds considered in the RESTART feasibility RCT.

Criterion	Critical feasibility outcome	Other feasibility and acceptability data relevant to the criterion		Proposed thresholds on critical outcome
1. Recruitment rate	Number of participants consented into the trial and randomised	Number of referrals per month Source of recruitment Number of participants contacted, number of participants assessed for eligibility Reasons for non‐eligibility or withdrawal of interest	  	Feasibility will be demonstrated where an average of at least 3 participants are recruited and randomised per month of active recruitment. If at least 2 participants are recruited per month, then a future trial will be feasible but additional strategies must be identified to support recruitment (e.g., informed by other feasibility data relevant to this criterion) If an average of 1 participant is recruited per month over the recruitment period (< 20 participants), feasibility within the current design will not be demonstrated

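### The planned sample size is 70 to be randomised in the abstract but 75 to be recruited in section 3.2, and nothing reconciles the two

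*Protocol article*

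**What the plan says.** The Method paragraph of the abstract states that "Seventy ARMS individuals with a history of trauma will be randomised" to one of the three arms. Section 3.2 (Participants) states: "This trial will aim to recruit 75 individuals who (1) meet ARMS criteria", and adds reported past trauma as the second condition. Section 3.2.1 sets the allocation: "TAU only at a ratio of 1:1:1".

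Section 5 (Outcomes) says that "the trial's primary outcomes will be the key feasibility indicators required to recommend progression towards a future larger‐scale trial". Recruitment is one of the four indicators. Table 2 defines its critical outcome as "Number of participants consented into the trial and randomised", and its top threshold is met where "an average of at least 3 participants are recruited and randomised per month of active recruitment". The thresholds for engagement, retention and fidelity are percentages. Section 6 plans no formal hypothesis tests of clinical effectiveness; it plans unadjusted mean differences between arms at 9 months with 80% confidence intervals.

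**The concern.** Both figures stand in the current text, in intact sentences, and each is presented as the plan. An article may leave the justification of its sample size to the full protocol, but this one states the size twice and gives two values.

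At stake is how completion of the trial is judged. If 70 are randomised, the abstract makes the trial complete and section 3.2 makes it 5 short. This deserves care here because the number randomised is itself the critical outcome for recruitment, and because a published protocol is where the target is fixed before results are known.

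**Working it through.** **Inputs.** N = 70 (abstract); N = 75 (section 3.2); three arms at 1:1:1 (section 3.2.1); 3 per month for the top recruitment threshold and 70% for the top retention threshold (Table 2); 80% confidence intervals (section 6). The article gives no power, effect size, SD or attrition allowance, so neither N can be reproduced from stated inputs.

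**Step 1: size of the gap.** 75 − 70 = 5, which is 5/75 = 6.7% of the larger figure and 5/70 = 7.1% of the smaller.

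**Step 2: can the text link the two?**
- *Loss between recruitment and randomisation.* Going from 75 to 70 needs a loss of 1 − 70/75 = 6.7%. No such loss is stated. The 75 are already described as meeting the ARMS and trauma criteria, so screening failures do not explain it. Table 2 counts being recruited and being randomised together.
- *Inflation for dropout, N/(1 − d).* From 70, d = 5% gives 73.7, so 74; d = 10% gives 77.8, so 78. Neither round allowance gives 75, and no allowance is stated.
- *Length of recruitment.* The lowest recruitment band pairs an average of 1 per month with fewer than 20 participants. If that is taken to mean about 20 months (an assumption), 3 per month gives 20 × 3 = 60, which is neither figure.

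**Step 3: what changes with N.**

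| Quantity | N = 70 | N = 75 |
|---|---|---|
| Expected per arm, N/3 | 23.3 | 25 |
| Expected in the two therapy arms, 2N/3 | 46.7 | 50 |
| Months to target at 3 per month, N/3 | 23.3 | 25 |
| Number retained that equals 70%, if all N are randomised | 49 | 52.5, so 53 |
| 80% CI half-width for a mean difference, 70% retained | 0.458 SD | 0.442 SD |

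The last row uses t(0.90) × √(2/n), with n = 0.70 × N/3 per arm: 16.33 for N = 70 and 17.5 for N = 75. With the normal quantile 1.2816 in place of t, the half-widths are 0.448 and 0.433 SD. The 70% retention used here is the Table 2 threshold, taken as an illustration and not as a forecast.

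**Step 4: what does not change.** The Table 2 cut-offs are 3, 2 and 1 per month for recruitment; 70% and 50% for engagement; 70% and 30% for retention; and 80% and 50% for fidelity. None names 70 or 75. The only total in the table, fewer than 20 participants, lies far below both.

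**The case against.** The strongest reply is that little depends on the difference. There is no power calculation to invalidate and no hypothesis test, the progression rules do not involve N, and the confidence interval half-width moves by only 0.016 SD. All of that stands, and it limits the size of the point. It does not remove the contradiction.

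A second reply is that 75 may be recruited and 70 randomised, since consent comes before the eligibility assessment. This is arithmetically possible, but it is stated nowhere, and both the description of the 75 and the joint count in Table 2 tell against it.

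A reader might also infer three stronger things that the article does not support:

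- *That there are two sets of primary outcome thresholds.* There are two enrolment targets. The thresholds are rates and percentages and are the same under both.
- *That the sample size determines when recruitment stops.* No stopping rule tied to N is stated, and Table 2 speaks of months of active recruitment and a recruitment period. The 23.3 and 25 months above are times to reach a target, not planned durations.
- *That 75 must be right because it divides by three.* A 1:1:1 ratio does not need a multiple of three; 23, 23 and 24 would be consistent with it. Permuted blocks whose size varies do not guarantee equal arms even at 75. Divisibility does not show which figure was intended.

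**Conclusion.** The point holds as an unreconciled planned sample size. One of the two figures is wrong, or the two count different things and the article does not say so. The gap is 5 participants: about 23 or 25 expected per arm, and 23.3 or 25 months to target at 3 per month. The precision of the between-arm estimates barely differs. No progression threshold and no planned analysis changes.

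It still needs correcting, because the planned number randomised is a basic design figure against which the finished trial will be read. The per-arm figures assume the stated 1:1:1 ratio and the precision figures assume 70% retention; the contradiction itself rests on no assumption. The article alone cannot show which figure is correct.

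**What to change.** Check the approved full protocol and state one randomised total in both the abstract and section 3.2. If 75 and 70 are both intended, say what each one counts (for example recruited and randomised) and give the reason for the difference.

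Keep the Table 2 thresholds as rates and percentages. Recasting them as counts on the planned N would mix under-recruitment with retention. For example, if 60 were randomised and 48 retained, retention would be 48/60 = 80% and would meet the 70% threshold, yet it would fail a fixed count of 53.

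The cost is one corrected figure or one added sentence, plus the check against the approved protocol. No design or analysis change follows from it.

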**Conclusions:**

If a large‐scale RCT is deemed feasible, it will be possible to establish whether EMDR and/or TF‐CBT represent beneficial treatments to augment existing evidence‐based care for individuals at ultra‐high risk for future psychosis, potentially reducing transition rates and improving clinical outcomes for ARMS individuals.

## Introduction

1

Past research has confirmed that traumatic life events can increase the risk of developing psychosis. Meta‐analytic findings suggest that exposure to various potentially traumatic events in childhood (e.g., bullying, sexual and physical abuse, etc.) is associated with a threefold increase in psychosis risk, with a population attributable risk of 33% (Varese et al. 2012). In parallel, a growing number of mediational and mechanistic studies have identified a range of psychological impacts of trauma that are plausibly implicated in the apparent association between trauma and various symptoms of psychosis (e.g., Williams et al. 2018; Alameda et al. 2021). This suggests that the emotional and psychological consequences of trauma may represent tractable treatment targets to reduce psychosis liability in at‐risk individuals with a history of trauma.

Recent systematic review and meta‐analyses have confirmed that trauma exposure is pervasive in individuals with At‐Risk Mental States (ARMS; Yung et al. 2005) and/or similar criteria for identifying individuals at ultra‐high risk for psychosis (e.g., Kraan et al. 2015). Trauma exposure in ARMS individuals is linked to comorbidities associated with heightened risk for psychosis transition, including poorer social and occupational functioning and more severe attenuated psychotic symptoms (Mayo et al. 2017; Brew et al. 2018; Peh et al. 2019). However, current treatments for preventing psychosis do not sufficiently target the impacts of trauma, and recent reviews have highlighted this as a critical area for future research to enhance treatment outcomes in this at‐risk group (Zarubin et al. 2023).

Several evidence‐based therapies specifically target the consequences of trauma, particularly trauma‐focused cognitive behavioural therapy (TF‐CBT) and eye movement desensitisation and reprocessing (EMDR). These therapies have a strong evidence base for treating post‐traumatic stress symptoms (NICE 2018) and are increasingly applied to other mental health sequelae of trauma, including psychosis (Hardy et al. 2024). Recent meta‐analyses have confirmed that these trauma therapies can improve post‐traumatic stress and, to a lesser extent, psychotic symptoms in people with psychosis (Brand et al. 2018). Yet, these promising developments have not led to parallel innovation in the treatment of trauma sequelae in people at clinical high risk for future psychosis. To date, early promising findings have been provided by a small RCT of an 8‐session EMDR intervention for people with prodromal psychosis and comorbid post‐traumatic stress disorder conducted in China (*N* = 57; Zhao et al. 2023) and a small non‐randomised trial (*N* = 14; Strelchuk et al. 2024) that offered ARMS individuals an ‘EMDR for psychosis’ intervention previously developed for first episode psychosis clients (Varese et al. 2021; Varese et al. 2024). Further research considering not only EMDR, but also other evidence‐based interventions for trauma (i.e., TF‐CBT) suitably adapted to maximise acceptability and effectiveness in clients with attenuated psychotic symptoms is urgently needed to inform the development of an evidence base for addressing the trauma‐related needs of individuals with ARMS.

## Aims

2

The primary aim of the current study is to determine the feasibility of conducting a future RCT to examine the clinical efficacy and mechanisms of action of TF‐CBT and EMDR interventions purposely adapted for people with ARMS. Feasibility will be assessed through four key indicators (trial recruitment, trial retention, EMDR/TF‐CBT treatment engagement, and EMDR/TF‐CBT treatment fidelity).

The secondary aims are to (1) examine the promise of efficacy of EMDR/TF‐CBT on important clinical outcomes and the acceptability of assessment instruments to investigate the efficacy and mechanisms of action of EMDR and TF‐CBT in this participant group, (2) gather data on the safety of EMDR and TF‐CBT in people with ARMS, (3) gather qualitative data to explore the acceptability of EMDR and TF‐CBT in trial participants, and (4) gather qualitative data from trial therapists, supervisors, and other professional stakeholders to explore their views on barriers and enablers of successful implementation of EMDR and TF‐CBT in future routine mental health care for the ARMS group.

## Methods

3

### Design

3.1

We will conduct a feasibility randomised controlled trial (RCT) with two nested qualitative studies. The trial will be a pre‐registered (ISRCTN76699092) single‐blind parallel group RCT with three arms: EMDR+treatment as usual (TAU), TF‐CBT+TAU, or TAU alone (see CONSORT diagram provided in Appendix S1). Key feasibility outcomes will be assessed by Research Assistants (RAs) at baseline and at a 9‐month post‐randomisation assessment, with further outcomes collected at 12‐month post‐randomisation via screening of medical records.

### Participants

3.2

This trial will aim to recruit 75 individuals who (1) meet ARMS criteria operationalised using the updated version of the Comprehensive Assessment of At‐Risk Mental States (CAARMS‐23; Yung et al. 2023) and (2) report exposure to past traumatic events in childhood or adulthood on the Trauma and Live Events questionnaire (TALE; Carr et al. 2018). The full inclusion and exclusion criteria of the RCT are listed in Table 1.

**TABLE 1 eip70095-tbl-0001:** Inclusion and exclusion criteria.

Inclusion criteria	16 years of age or older Meeting ARMS criteria as defined by the CAARMS Capacity and willingness to provide informed consent Reported exposure to at least one potentially traumatic life events, as assessed by the TALE
Exclusion criteria	Under 16 years of age Non‐English speaking or requiring an interpreter for the intervention (the assessment battery at present can only be delivered in English) Evidence of recent or past transition from ARMS status to first episode psychosis (FEP), operationally defined as meeting CAARMS transition criteria (i.e., history of a treated or untreated psychotic episode of 1 week's duration or longer) and/or previous or current treatment with antipsychotics at dose of over 5 mg of haloperidol or equivalent for over 3 weeks Judged by the assigned care‐coordinator/responsible clinician and the research team as not sufficiently clinically stable to engage safely in a clinical trial of trauma‐focused therapy (e.g., acutely suicidal and suicide attempt in the previous 2 months; in a current mental health crisis; not in stable housing).

*Note:* ARMS = at risk mental state; CAARMS = comprehensive assessment of at risk mental states (Yung et al. 2005); TALE = Trauma and Life Events checklist (Carr et al. 2018).

Prospective participants will be identified through Early Detection and Intervention Teams (EDIT) and Early Intervention for Psychosis (EIP) services at three UK National Health Service (NHS) mental health trusts in the North West of England, and other mental health services that interface with EDIT/EI services and provide support to individuals who may meet ARMS criteria (e.g., student mental health services; complex primary care psychological therapy services, etc.). ARMS individuals who participated in recent non‐interventional studies by the research team and consented to further contact for research involvement purposes will also be approached. Trained RAs will obtain informed consent prior to an eligibility assessment using the CAARMS‐23 and the TALE.

#### Randomisation and Allocation Concealment

3.2.1

Participants will be randomly allocated to either (1) EMDR+TAU, (2) TF‐CBT+TAU, or (3) TAU only at a ratio of 1:1:1. Randomisation will be independent and concealed via an online pseudo‐random list with random permuted blocks of varying sizes. Allocation will be concealed from the RAs conducting follow‐up assessments. If an RA becomes “unblinded” to a participant's allocation during the study, where possible, the participant will be allocated to another RA. Where this is not possible, interview‐based measures will be recorded with participant consent, and the measure will be scored by blinded RAs.

## Interventions

4

### Comparator: TAU

4.1

TAU will be in line with all standard and individually prescribed clinical interventions as directed by national clinical guidelines for psychosis/ARMS (National Institute for Health and Care Excellence [NICE] 2013, 2014) and the participants' clinical teams. In EDIT services and ARMS pathways within EIP services, support provided to ARMS individuals typically includes active monitoring of prodromal symptoms and the offer of preventive interventions for psychosis, in particular Cognitive Behavioural Therapy. However, TAU for ARMS individuals may differ depending on additional clinical needs and whether service users are referred to and/or managed by other primary or secondary care mental health services over the course of the RCT. In no case will the trial team interfere with teams' clinical decision making by asking to withhold referrals or interventions that would be offered to participants as part of their usual care, including other active psychological interventions. The uptake of interventions comprised in TAU will be documented via reviews of participants' medical notes for up to 12 months post‐randomisation.

### 
EMDR Intervention

4.2

Participants allocated to the EMDR+TAU arm will receive up to 24 sessions of EMDR over a 9‐month treatment window, in addition to TAU. Each session will last up to 90 min and will be audio/video‐recorded for fidelity monitoring purposes when participants consent to this. The specific protocol used as part of this trial has already been evaluated and implemented successfully in other feasibility trials conducted by the research team with clients who have already transitioned to FEP (for further details on this treatment approach, see Varese et al. 2021; Varese et al. 2024), which will be gradually refined over the course of this trial to maximize acceptability and clinical benefit for ARMS participants.

### 
TF‐CBT Intervention

4.3

Participants allocated to the TF‐CBT+TAU arm will receive up to 24 sessions of TF‐CBT delivered over a 9‐month treatment window, in addition to TAU. Each session will last up to 90 min and will be audio‐recorded for fidelity monitoring purposes when participants consent to this. The TF‐CBT intervention delivered as part of this trial will be adapted for delivery in individuals with an ARMS from a similar, annualised intervention already developed for a definitive trial of trauma‐focused therapy for individuals with schizophrenia‐spectrum disorders by integrating intervention strategies and models for the treatment of PTSD and psychotic symptoms (for further details, see Peters et al. 2022).

### Procedures to Monitor and Promote EMDR and TF‐CBT Fidelity and Adherence

4.4

The treatment will be delivered by EMDR‐ and CBT‐trained therapists who have experience in working with people with psychosis, ARMS, and complex trauma. All therapists will attend an initial 3‐day training workshop in the EMDR protocol and a separate 3‐day training in the TF‐CBT protocol used as part of the trial. Throughout the study, trial therapists will attend separate EMDR and TF‐CBT supervision sessions with experienced therapy supervisors. Treatment fidelity will be ensured in two ways. First, the EMDR and TF‐CBT supervisors will rate a quasi‐random selection of therapy recordings (for up to 10% of the therapy sessions delivered for each experimental arm of the trial) using the EMDR Fidelity Rating Scale (EFRS; Korn et al. 2017) and the adapted version of the Cognitive Therapy Scale—Revised (CTS‐R) developed by Peters et al. (2022), which will be further modified as needed to capture additional adaptation related to ARMS‐specific work. This will ensure that all therapists involved in the RCT demonstrate at least acceptable adherence to EMDR and TF‐CBT when delivering these therapies to ARMS clients. Secondly, after each therapy session, therapists will be asked to complete a standardised session record form to monitor session content and monitor adherence against the EMDR and TF‐CBT protocols used in the trial.

